### Study design

We have conducted a randomised controlled feeding study with cross-over design in which households were provided with flour milled from genetically and agronomically biofortified grain (Zincol-2016/NR-421) or control grain (Galaxy-2013). Galaxy-2013 was chosen for the control grain because it is widely cultivated across the country and is popular among farmers due to its higher yield. It did not receive Zn-containing fertilisers. Zincol-2016 (formerly known as NR-421 strain/line) was bred by the National Agriculture Research System, Pakistan with the support of HarvestPlus and approved by the Punjab Seed Council, Pakistan in 2016.^18^ The grain for both the genotypes was sown at a farm in District Vehari, Punjab, Pakistan in November 2016 and harvested in May 2017 by our project partner, Fauji Fertilizer Company (FFC) Limited. During the growing period, Zn-enriched fertiliser (Zn 13% as EDTA Zn) was applied to Zincol-2016 genotype at 1.25 kg/ha through injection into the irrigation system. This was followed by five foliar sprays of Zn (ZnSO_4_·H_2_O 33% Zn) applied at 1 kg/ha of product dissolved in 250 L of water and sprayed per hectare at the booting stage. Analyses revealed that the pre-harvest Zn concentration in grains were 62 (SD 7.7) mg/kg and 27 (SD 4.3) mg/kg for the biofortified and control grain, respectively. The grain was transported from the farm to the study field site in clearly labelled sacks (control and biofortified). The bags of grain were manually cleaned (hand removal of debris, stones, stalks), mixed and milled at a local facility. Care was taken to avoid cross-contamination from previously milled grain. Samples of grain from each sack (top, middle and bottom) were retained for analysis.

The intervention trial was composed of a 2-week baseline equilibration period and two 8-week intervention/control periods. The baseline period started on 1 October 2017. During the baseline period, all the participating households were provided with control flour. After 2 weeks, group A received biofortified flour and group B received control flour. After 8 weeks, the two groups will cross over, with group A receiving control flour and group B receiving biofortified flour for the final 8 weeks (figure 1). Freshly milled flour was provided on a fortnightly basis for consumption by the entire household (average seven individuals, including children). Families will be asked not to consume any other flour within the household during the 18-week study period. Compliance was monitored at each flour distribution time point through interview with the head of the household. The number of meals consumed outside the household by the primary study participant (woman of childbearing age) was recorded. Our previous knowledge of this community indicates that, other than community events such as weddings, it is unusual for women to eat outside the home.

### Primary outcome measures

Flour is used primarily for making roti and chapati in this community. The contribution of the total Zn intake from foods made from flour will be determined using 24-hour recall, coupled with food composition databases (eg, WinDiets 2005 Research software, Robert Gordon University, UK). In addition, a selection of composite meal samples will be analysed. The impact of consuming the biofortified flour on the Zn status of women of childbearing age will be assessed by measuring plasma Zn concentration on ICP-MS analysis, DNA fragmentation by Comet assay, and hair and nail Zn concentration by ICP-MS. In addition, we will measure concentrations of inflammatory biomarkers C-reactive protein (CRP) and alpha 1-acid glycoprotein that will be used to adjust plasma Zn concentration if required.^19^

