The primary aim of this study is to measure the impact of consuming flour made from the recently released high-Zn wheat grain variety Zincol-2016/NR-421 on dietary Zn intake and biomarkers of Zn status in a low-resource rural community setting in Pakistan. The secondary aim is to evaluate the potential usefulness of new biomarkers of Zn status. These aims will be achieved through conducting a randomised controlled feeding study with a cross-over design. Comparison of outcome measures will be made following consumption of flour made from the biofortified wheat variety, Zincol-2016/NR-421, and the control, non-biofortified variety, Galaxy. The trial has been registered with the ISRCTN registry, study ID ISRCTN83678069.^16^

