Ten households from each cluster were randomly selected. The head of the household was approached, the purpose of the study explained and, if eligible, the family invited to participate in the trial. If the head of the household declined, another house from the cluster was randomly selected and the invitation process repeated. Inclusion criteria were the household included a woman aged 16–49 years who was neither pregnant nor breastfeeding, and not currently consuming nutritional supplements. When there was more than one eligible woman in the household, one was conveniently selected with agreement from the head of the household. There were no additional exclusion criteria. Following informed consent, each household was assigned to treatment arm A or B (refer to figure 1) using a block design. A sample size of 40, 95% significance level (two-sided) and 90% power, will enable an increase in plasma Zn concentration of 3.1 µg/dL to be detected. The target was to recruit 50 households (50 eligible women) to be able to accommodate a 20% attrition rate during the 18-week study. The project manager led the recruitment process because he is known to the community through previous health-related projects associated with the Abaseen Foundation PK (AFPK), a local non-governmental organisation and key member of this project team, along with its sister organisation Abaseen Foundation UK. There is a high level of trust and cooperation between community members and the AFPK who operate the health centre that serves this Union Council; therefore, high levels of participant enrolment has been achieved. The project manager was responsible for allocating participants to each arm of the cross-over trial using a block design. Only the project manager had access to this information.

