## Statistical analysis plan

The analysis will be performed as intention to treat. Descriptive statistics will summarise participants’ characteristics and outcome measurements at each time point, using methods appropriate for the type of data. Most study outcome measurements will be quantitative data. The primary outcome, plasma Zn concentration, was collected at five time points (baseline, weeks 4, 8, 12 and 16). After adjustment for inflammatory markers and as described above, the primary outcome will be assessed in two type comparisons:

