### Comparisons between groups A and B

To answer the primary research question of determining the effectiveness of consuming flour made from agronomically biofortified wheat for improving Zn status, study outcomes will be compared between groups A and B at week 8 and week 16, complemented with comparisons at interim collection points, week 4 and week 12. The pairwise comparisons will be done using independent-samples t-test or Mann-Whitney U test as appropriate. Linear mixed modelling will be used for adjusted analyses to account for the baseline, repeated measurements and relevant covariates. Similar analysis will be done for all secondary outcomes measuring Zn status.

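### Five measures are listed as primary outcomes, but the analysis section and the sample size recognise only plasma Zn, and no single plasma Zn comparison is named as decisive

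*Protocol article*

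**What the plan says.** The section Primary outcome measures opens with intake: "The contribution of the total Zn intake from foods made from flour will be determined using 24-hour recall". It then says that Zn status will be judged by "plasma Zn concentration on ICP-MS analysis, DNA fragmentation by Comet assay, and hair and nail Zn concentration by ICP-MS". The subsections on diet, plasma, DNA fragmentation, hair and nails follow under that heading; the next heading of the same rank is Additional outcomes, which starts with anthropometry. Five measures are therefore presented as primary.

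The Statistical analysis plan section says otherwise: "The primary outcome, plasma Zn concentration, was collected at five time points". Its subsection on comparisons between groups A and B ends: "Similar analysis will be done for all secondary outcomes measuring Zn status". The same subsection answers the primary research question by comparing the groups at weeks 8 and 16, with weeks 4 and 12 as interim comparisons. It uses independent-samples t-tests or Mann-Whitney tests, and adds a linear mixed model for adjusted analyses.

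Under Study setting and recruitment the trial is sized on plasma Zn only: "A sample size of 40, 95% significance level (two-sided) and 90% power", for an increase of 3.1 µg/dL.

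The Introduction gives the primary aim as the effect "on dietary Zn intake and biomarkers of Zn status in a low-resource rural community setting in Pakistan", and adds: "The secondary aim is to evaluate the potential usefulness of new biomarkers of Zn status".

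**The concern.** The same measures are primary in one section and secondary in another. Apart from plasma Zn, the Zn-status measures described are DNA fragmentation, hair Zn and nail Zn, so the secondary outcomes in the analysis section must be measures that the outcome section lists as primary. A separate analysis plan could fill a gap, but it cannot make both statements true.

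A second ambiguity lies inside plasma Zn. The two end-of-period comparisons carry equal weight, and the article does not say which one settles the question or what follows if they disagree.

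What is at stake is which result can be reported as the trial's primary finding. As the text stands, a favourable result on another marker, or at one of the two weeks, could be presented as primary with some support from the article.

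**Working it through.** **Inputs.** From Study setting and recruitment: 40 evaluable women, 90% power, two-sided test, 3.1 µg/dL, 20% attrition, 50 households. The stated 95% significance level is read as alpha = 0.05. From Primary outcome measures: five measures. From Comparisons between groups A and B: weeks 8 and 16 as main time points, weeks 4 and 12 as interim. The correlations below are assumptions; the article gives none.

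**The plan's own figure.** Attrition: 40/(1 − 0.20) = 50, which matches. The power step cannot be reproduced, because the article gives no SD (this is not held against it). Back-solving for a within-woman comparison by the normal approximation: SD of the difference = 3.1 × √40/(1.960 + 1.282) = 6.05 µg/dL.

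**Reading 1: plasma Zn is the only primary outcome.** There is no inflation across measures. Across weeks, at 5% two-sided each:
- Weeks 8 and 16, independent: 1 − 0.95² = 9.75%. By simulation, about 9.0% at correlation 0.5 and 7.1% at 0.9.
- All four weeks, independent: 1 − 0.95⁴ = 18.5%.
- False claim of benefit only, 2.5% per test: over two weeks 1 − 0.975² = 4.9% if independent, and never above 2 × 2.5% = 5% at any correlation.

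**Reading 2: all five are primary and any one suffices, at one time point.**
- Independent: 1 − 0.95⁵ = 22.6%.
- Simulation of five equally correlated two-sided tests (400,000 draws):

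| Assumed correlation | At least one false positive |
|---|---|
| 0.3 | 20.9% |
| 0.5 | 18.2% |
| 0.7 | 14.9% |
| 0.9 | 10.2% |

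**What Reading 2 would need if adjusted.** Bonferroni, as an illustration: 0.05/5 = 0.01 per measure.
- Power for plasma Zn at N = 40: Φ(1.960 + 1.282 − 2.576) = Φ(0.666) ≈ 75%.
- Detectable difference at 90% power: 3.1 × (2.576 + 1.282)/(1.960 + 1.282) = 3.69 µg/dL.
- N for 90% power at 3.1 µg/dL: 40 × (3.858/3.242)² = 56.6, so 57 evaluable, and 57/0.80 = 71.25, so 72 recruited.

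Under this adjustment the stated 40 evaluable and 50 recruited would be too few. They fit plasma Zn as the sole primary outcome.

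**Reading 3: all five must succeed.** Type I error is not inflated, but power falls below that for plasma Zn alone. The article gives no sign of this rule.

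**The case against.** The best defence is that the article largely settles the hierarchy itself. The analysis section names one primary outcome, the sample size rests on it, and the remaining Zn-status measures are called secondary. The heading Primary outcome measures then reads as a loose grouping set against Additional outcomes. This stands as a guide to the authors' probable intention, and it shows which way to repair the text. It does not remove the conflict.

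It is also fair to say that a multiplicity rule is commonly left to the full analysis plan. Its absence is not the point here; the incompatible labels and the unnamed decisive comparison are.

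Stronger readings are tempting, but the documents do not support them:
- **Ten tests.** A reader might multiply five measures by two weeks and reach 1 − 0.95¹⁰ = 40.1%. But the Nail and hair analysis section collects nails at baseline and then about 7 months after the start of each phase, so there is no nail test at weeks 8 and 16. Intake is not a status measure and is not clearly covered by the sentence that extends the analysis to secondary outcomes.
- **Any one suffices.** A reader might take 22.6% as the trial's actual error rate. No such success rule is stated, so the figure is conditional.
- **Error above 5% on every reading.** For plasma Zn at weeks 8 and 16, a false claim of benefit stays at or below 5%.
- **A biomarker under evaluation cannot also be evidence of effect.** That is opinion. The primary aim openly includes biomarkers in the plural. The Introduction names the Comet assay and nail laser ablation as emerging techniques but treats hair Zn separately, and the article cites earlier evidence that DNA fragmentation falls after Zn supplementation. What remains is a caution: a null result on a marker still being evaluated cannot separate an ineffective flour from an insensitive marker.

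**Conclusion.** The point holds as an inconsistency in the current text. Five measures appear as primary in one section, while the analysis section and the sample size recognise plasma Zn alone, and within plasma Zn the decisive comparison is not named.

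The size depends on the reading. With plasma Zn alone, error across weeks 8 and 16 is up to 9.75% in either direction, assuming independent two-sided 5% tests. With all five primary and any one sufficient, it is 22.6% under independence and about 10% to 21% at assumed correlations of 0.9 to 0.3. The first reading is much the likelier, so the practical harm is uncertainty over which result counts rather than a demonstrated loss of error control. The text should be corrected before results are known; the section on data collection still describes the laboratory analysis as to come.

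**What to change.** 1. Under Primary outcome measures, name plasma Zn as the sole primary outcome. Relabel dietary Zn intake, DNA fragmentation, hair Zn and nail Zn as secondary, reported with estimates and confidence intervals. The Introduction's primary aim can keep its breadth if the outcome section makes clear that plasma Zn carries the decision.
2. Under Comparisons between groups A and B, name one decisive comparison: the biofortified-versus-control effect on plasma Zn, estimated from both periods in the mixed model already planned, with period and sequence terms, and tested once at two-sided 5%. The end-of-period samples (weeks 8 and 16) are the natural contrast, since the article treats weeks 4 and 12 as interim. Keep the week-specific comparisons as supportive.

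**Cost.** Sample size, sampling and laboratory work are unchanged. The first step is wording only. The second changes the primary analysis: the separate week-8 and week-16 t-tests become supportive, and combining the periods assumes that carry-over into period 2 is negligible, which should be stated. A significant result on another marker, or at a single week, can no longer be called the primary finding.

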#### Dietary analysis

Dietary nutrient intake will be assessed by analysing the 24-hour recalls that were collected by interviewing the women participants by the study nutritionist, who has local knowledge of the foods consumed and speaks Pushto, the local language. From our previous research,^17^ we know that the local diet is very limited in variety and monotonous and therefore a total of five recall interviews, taken at each of the sampling points (figure 1), will give a good estimate of typical nutrient intake. Portion sizes will be estimated using household measures, using items that are familiar to the households (eg, plates, cups, spoons). Macronutrient and micronutrient composition, plus phytate will be calculated from appropriate food composition databases. In addition, a selection of commonly consumed composite meals will be analysed for mineral, macronutrient and phytic acid concentration. During this interview, the nutritionist also collected data regarding adverse health-related events since the last measurement time point. Mothers were also asked to report on the frequency and duration of diarrhoeal episodes among children in the household. Any major concerns were reported to the Health Centre Doctor for follow-up.

#### Biomarkers of Zn status

Tissue samples were collected from participants attending the Health Centre at five time points: baseline, middle and end of intervention phase 1, and middle and end of phase 2 (figure 1).

#### Plasma Zn concentration

Whole blood was collected into trace element–free tubes (BD Diagnostics, Switzerland) and the plasma separated by centrifugation within 40 min. Plasma 300 µL aliquots were transferred into Eppendorf tubes and stored at −20°C. Plasma samples will be shipped on dry ice to the University of Nottingham for analysis by ICP-MS.

#### DNA fragmentation analysis

DNA fragmentation (measured using the Comet assay) has been shown to decrease following dietary Zn supplementation.^20^ Whole blood was collected by venous blood draw. Duplicate samples of 50 µL of whole blood was mixed with 50 µL cryopreservation buffer (85% RPMI, 15% DMSO) in a cryovial and stored in a cryopreservation container in a fridge for up to 8 hours. Samples were transferred from the health centre to Khyber Medical University (KMU) on ice and placed in a −80°C freezer overnight (up to 12 hours), then transferred to liquid nitrogen for storage until samples at all five time points have been collected. DNA fragmentation will be quantified using the method of Singh *et al*,^21 22^ and Comet Assay IV Lite software (Perceptive Instruments, London, UK) for tail moment measurement.

#### Nail and hair analysis

Whole hairs were collected by combing through the hair and collecting individual hairs from the comb, making sure that the tag (cells from follicle) is attached to the proximal end of the hair. Nail samples were collected at baseline. Nail samples will be collected two more times at approximately 7 months (average time taken for a nail to grow from formation in the nail bed to the tip of the finger) from the start of phase 1 and phase 2. The Zn concentration of hair and nail samples will be determined using laser-induced breakdown spectroscopy^23^ at NeurobioTex (Galveston, Texas, USA).

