**Methods and analysis:**

We are conducting a double-blind, randomised controlled feeding study with cross-over design in a low-resource setting in Pakistan. Households were provided with flour milled from genetically and agronomically biofortified grain (Zincol-2016/NR-421) or control grain (Galaxy-2013). Fifty households were recruited. Each household included a woman aged 16–49 years who is neither pregnant nor breastfeeding, and not currently consuming nutritional supplements. These women were the primary study participants. All households were provided with control flour for an initial 2-week baseline period, followed by an 8-week intervention period where 25 households receive biofortified flour (group A) and 25 households receive control flour (group B). After this 8-week period, groups A and B crossed over, receiving control and biofortified flour respectively for 8 weeks. Tissue (blood, hair and nails) have been collected from the women at five time points: baseline, middle and end of period 1, and middle and end of period 2.

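### Follow-up nail samples are timed from the start of each phase, so on average the first misses the intervention and the second mainly reflects the preceding phase

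*Protocol article*

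**What the plan says.** The Nail and hair analysis section states that "Nail samples were collected at baseline". It then sets two further collections: "Nail samples will be collected two more times at approximately 7 months (average time taken for a nail to grow from formation". Both are counted "from the start of phase 1 and phase 2". It explains the 7 months as the "average time taken for a nail to grow from formation in the nail bed to the tip of the finger".

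Study design dates the start of the baseline period to 1 October 2017. Baseline lasts two weeks, with control flour for everyone. Two 8-week periods follow: group A has biofortified flour and group B control flour in the first, and they swap in the second. No washout is described.

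Other places that bear on nails:

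- The abstract says "Tissue (blood, hair and nails) have been collected from the women at five time points", against baseline plus two in Nail and hair analysis.
- Primary outcome measures names ICP-MS for hair and nail zinc. Nail and hair analysis names laser-induced breakdown spectroscopy.
- The section on comparisons between groups A and B closes with "Similar analysis will be done for all secondary outcomes measuring Zn status".

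**The concern.** A growth time from nail bed to fingertip tells us how far back to look from the day of collection. Counting that time forward from the first day of a phase brings to the tip the nail formed on that first day. Nail formed during the following eight weeks has not yet arrived, and anything already beyond the tip is older.

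At stake is the nail part of the secondary aim, which is to evaluate newer zinc biomarkers; the Introduction names nail zinc among them. A biomarker that works could look unresponsive, or could appear to move the wrong way, only because of when the nail was taken. Group B's period on biofortified flour would on average not be sampled at all.

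**Working it through.** **Inputs from the article.** Baseline starts 1 October 2017; periods of 2, 8 and 8 weeks (total 18, as stated); flour by group and period as above; average growth time T = 7 months, counted from each phase start.

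**Assumptions (not in the article).** The sample is nail from the fingertip outward and holds g weeks of growth. Nail zinc follows the flour eaten when the nail formed, with true effect d (biofortified minus control). One month is 30.44 days, so T = 213 days = 30.4 weeks, and an 8-week phase is 8/30.4 = 26% of the grow-out.

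**Step 1: dates.**
- Phase 1 starts 1 Oct + 2 weeks = 15 Oct 2017.
- Phase 2 starts (phase 1 ends) 15 Oct + 8 weeks = 10 Dec 2017.
- Phase 2 ends 10 Dec + 8 weeks = 4 Feb 2018.
- Collections: 15 Oct + 213 days ≈ 16 May 2018; 10 Dec + 213 days ≈ 11 July 2018.

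**Step 2: formation window** = from (collection − T − g) to (collection − T).
- First sample: ends 15 Oct 2017. With g = 4 it runs from 17 Sep to 15 Oct: half pre-study diet, half baseline control flour, no phase 1 nail.
- Second sample: ends 10 Dec 2017. With g = 4 it runs from 12 Nov to 10 Dec: all phase 1. This holds for any g up to 8 weeks.

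**Step 3: contrasts if each sample is analysed under the phase it is counted from.** Let p1 and p2 be the shares of nail formed in phases 1 and 2. First sample: A − B = (p1 − p2)d. Second sample: B − A = (p2 − p1)d. The cross-over estimate is their mean. With T exactly 7 months: 0, −d and −d/2.

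**Step 4: between-woman variation in T.** The article gives no spread. Simulated with a normal distribution around 7 months:

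| Growth in sample | SD of T | First sample | Second sample | Cross-over |
|---|---|---|---|---|
| 4 weeks | 0 | 0 | −1.00d | −0.50d |
| 2 weeks | 0.5 month | +0.33d | −0.34d | −0.01d |
| 4 weeks | 0.5 month | +0.21d | −0.57d | −0.18d |
| 8 weeks | 0.5 month | +0.11d | −0.67d | −0.28d |
| 2 weeks | 1 month | +0.37d | −0.14d | +0.11d |
| 4 weeks | 1 month | +0.30d | −0.27d | +0.02d |
| 8 weeks | 1 month | +0.20d | −0.38d | −0.09d |

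In the 4-week rows the second sample is 78% phase 1 and 21% phase 2 nail at SD 0.5 month, and 58% and 31% at SD 1 month.

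**Step 5: a different common T (g = 4, no spread).**
- 6 months: each sample falls wholly in its own phase (+d, +d).
- 6.5 months: the first is 54% phase 1 and 46% baseline (+0.54d). The second is 54% phase 2 and 46% phase 1 (+0.08d).
- 7.5 months: the first is all pre-study and the second all phase 1 (0, −d).

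**Step 6: counting from phase end.** Collections fall at 10 Dec + 213 days ≈ 11 July 2018 (phase 1 sample) and 4 Feb + 213 days ≈ 5 September 2018 (phase 2 sample). With T exactly 7 months and g up to 8 weeks, each is 100% own-phase nail. With g = 4, the own-phase share is 78% at SD 0.5 month and 58% at SD 1 month. If diet after the study is the same in both groups, the contrasts are:
- SD 0.5 month: 0.78 − 0.21 = +0.57d and 0.78 − 0.01 = +0.77d; mean +0.67d.
- SD 1 month: 0.58 − 0.31 = +0.27d and 0.58 − 0.09 = +0.49d; mean +0.38d.

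The result is still diluted, but the sign is right in both samples.

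**The case against.** A reader might infer that the treatment labels on the nail samples are reversed. The article does not support that as a statement of fact. It does not say which flour each nail sample will be assigned to, nor that the sample is a clipping, nor which part of the nail is read. Even on the worst case, reversal concerns only the second follow-up sample; the first carries little contrast of either sign. The growth time is also approximate and an average, so variation between women mixes the phases, and a 6-month growth time would make the schedule work. All of this stands, and it limits the claim to a range from dilution to sign reversal at one sample.

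It does not remove the problem. The article itself gives 7 months and ties each collection to a phase. Whatever label is used, on that figure the first sample holds little contrast and phase 2 is not targeted. A laser reading at a chosen point would help only if nail still proximal to the tip were available; along the free edge it reaches only older nail.

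Three further inferences should be resisted:

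- That the primary result is at risk. Nail zinc appears under Primary outcome measures, but the Statistical analysis plan names plasma zinc as the primary outcome.
- That the planned analysis cannot be run on nails. A similar analysis need not use the same weeks, and three samples still allow a comparison of A with B adjusted for baseline.
- That the Biomarkers of Zn status section also claims five nail collections. It speaks of tissue samples without naming nails; only the abstract lists nails with five time points.

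**Conclusion.** The timing rule is wrong on the article's own definition. Counting an average 7-month growth time from phase start yields nail formed, on average, at or before that start. The first follow-up sample mostly reflects baseline or pre-study diet in both groups. The second mainly reflects phase 1, when each group ate the opposite flour to phase 2. If the samples are analysed under the phases they are counted from, the nail contrast is about 0 and then −d with no spread in growth time. At an assumed SD of 0.5 to 1 month and four weeks' growth it is +0.21d to +0.30d, then −0.57d to −0.27d, and the cross-over estimate lies between −0.18d and about 0.

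This rests on nail being taken at or beyond the tip, on nail zinc following the flour at formation, and on 7 months being close to the true average. The consequence is confined to the nail biomarker evaluation. The fault lies in a rule that the article states, so it is more than detail left to a fuller document. The conflicts over the number of nail time points and the assay are separate, genuine inconsistencies; neither is evidence for the timing error.

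**What to change.** Count the 7 months from the end of each phase. Phase 1 ends when phase 2 starts, so the collection at about 11 July 2018 stays and serves as the phase 1 sample. The collection at about 16 May 2018 is replaced by one at about 5 September 2018 for phase 2. The number of collections is unchanged; the cost is one date about 16 weeks later and the longer follow-up that this needs.

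In the analysis, assign flour exposure by estimated formation date, state the nail segment and growth time assumed, and acknowledge that variable growth will still mix phases to some extent.

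The article writes these collections in the future tense. If they have since been made, assign the existing samples by formation date and report phase 2 nail data as unavailable. That needs no new sampling, but it loses the cross-over for nails.

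Separately, reconcile the number of nail time points (five in the abstract; baseline plus two in Nail and hair analysis) and the nail assay (ICP-MS in Primary outcome measures; laser-induced breakdown spectroscopy in Nail and hair analysis). These are changes of text only.
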